In traditional Chinese medicine (TCM), *qi* usually refers to life energy, which manifests simultaneously on the physical and mental-spiritual levels [24]. The quintessence of TCM is syndrome differentiation and treatment. From the perspective of TCM, CRF is recognized as deficiency syndrome pattern, which is mainly caused by deficiency of *qi* and disharmony of *yin* and *yang* [25]. Many patients with CRF have symptoms of fatigue, listlessness, shortness of breath, and weak pulse after chemotherapy. These symptoms are similar to the syndrome of *qi* deficiency in TCM theory. According to TCM theory, this herbal prescription has been identified as an effective medication to tonify *qi* for reducing general weakness [23].

Ginsenosides, extracted from ginseng, and ophiopogonis, extracted from dwarf lilyturf tuber, are the principal constituents responsible for the pharmacological activities in SMI [26]. There are several studies on ginseng for the treatment of fatigue, and studies in mice have shown that ginseng can alleviate fatigue [27, 28]. One large study evaluating ginseng in combination with vitamins and minerals in 232 patients who had functional fatigue for over 10 years concluded that the ginseng formula improved fatigue symptom scores statistically significantly more than vitamin placebo [29]. An abstract presented at the 2003 meeting of the American Society of Clinical Oncology evaluated ginseng in people with cancer. It reported that ginseng significantly improved total and average fatigue levels, even though the sample size was quite small (*n* = 20) [30].

This study aims to assess the efficacy and safety of the addition of SMI to conventional therapy for advanced NSCLC patients undergoing chemotherapy. The primary hypothesis is that the SMI plus conventional therapy (here our treatment group) will experience less fatigue, as measured using Functional Assessment for Chronic Illness Therapy-Fatigue (FACIT-F) subscale scores, than conventional therapy alone (here our control group). Secondary objectives are to evaluate the efficacy of SMI on the following factors: symptom distress scores, depression, sleep disorders, quality of life (QOL), levels of inflammatory indicators, and adverse events (AEs).

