### Safety

An independent Data and Safety Monitoring Committee will evaluate the progress of the study and assess the safety data, as requested during the study. Adverse events (AEs) will be defined as any undesirable experience participants endure during the trial period, regardless of whether or not it is associated with the intervention. Participants will be instructed to report AEs to the research team, and a research nurse will monitor participants for potential occurrences of AEs. All details of AEs, such as time of occurrence, severity, management, and causality to the intervention, will be recorded on case report forms. All AEs will be followed up from the date they are brought to the investigator’s attention until resolution. Severe AEs must be reported to both the GPHCM Data and Safety Monitoring Committee and the GPHCM Ethics Committee within 24 h. Severe AEs will be defined according to the International Conference on Harmonization guidelines [41]; any adverse event will be regarded as serious if it results in death, is life-threatening, requires hospitalization or prolongation of existing hospitalization, or results in persistent or significant disability or incapacity.

To assess safety, we will perform the following tests on participants at the screening phase (baseline) and on day 5 (the end of the intervention): routine blood, routine feces, routine urine, liver, and kidney function, and electrocardiography. Safety will be assessed according to the National Cancer Institute Common Terminology Criteria for Adverse Events, version 4.0.

In particular, we will pay attention to adverse drug reactions (ADRs) associated with SMI. Because of its effectiveness, the scope of diseases treated with SMI has gradually broadened, and reports of associated adverse reactions have increased correspondingly. The number of published literatures has ranked SMI ninth for ADRs in 33 varieties of Traditional Chinese Medicine injections in the 2004 edition of the National Essential Drugs List (2004 edition) in China [42].

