Current evidence shows that SMI has a lower rate of ADRs. However, a systematic review of ADRs associated with SMI since 1995 showed that ADR cases were mainly systemic reactions (allergic shock), skin lesions (urticaria and pruritus), and local pain [43]. Because most ADRs occurred in the first 30 min of the first SMI administration, we suggest that patients should be closely observed during this period. Meanwhile, for patients who had continuous treatment with SMI, there is a need for close attention. ADR severity for each event as classified according to World Health Organization guidelines is shown in Table 1 [44].

**Table 1 Tab1:** Classification of adverse drug reaction (ADR) severity for Shenmai injection

Classification of ADR severity	
Class I	ADRs are deadly or life-threatening; patients need to be withdrawn from drugs and treated immediately; or ADRs last for more than 1 month.
Class II	Patients have pathologic and physiologic changes and must be withdrawn from drugs and treated; or ADRs last for more than 7 days.
Class III	Patients cannot endure the ADRs and must be given a lower dose or withdrawn from drugs; patients improve after symptomatic treatment.
Class IV	Patients can endure the ADRs, and no lowering of dose or drug withdrawal is necessary. Whether without treatment or through symptomatic treatment, patients improve

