### Statistical analysis

Efficacy and safety analyses will be conducted according to the intention-to-treat principle. All statistical analyses will be performed using Statistical Packages of Social Sciences software (SPSS; version 19.0). All results made in this study are based on two-sided tests. A *P* value < 0.05 will be considered statistically significant. Continuous data will be presented as means and standard deviations and compared using the independent *t* test or Wilcoxon’s rank sum test, while categorical data will be presented as percentages or frequencies and compared using the chi-square or Fisher’s exact test. Data for subjects who meet the dropout criteria (i.e., incidence of serious AEs, < 80% compliance with the protocol, incomplete data that could influence the trial, reluctance to continue the study, large error in protocol, or deviation from the protocol) will be excluded. Missing values will be implemented by multiple imputations.

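### The protocol promises intention-to-treat for safety, yet excludes patients with a serious adverse event without exempting the safety analysis

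*Protocol article*

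**What the plan says.** All of the analysis text is one paragraph, the Statistical analysis section of the protocol article. Near its start it says: "Efficacy and safety analyses will be conducted according to the intention-to-treat principle". Further on it gives the exclusion rule, which begins "Data for subjects who meet the dropout criteria (i.e., incidence of serious AEs", continues through compliance below 80%, incomplete data and unwillingness to go on, and ends "large error in protocol, or deviation from the protocol) will be excluded". The next sentence assigns missing values to multiple imputation. The section names no separate safety population and does not say which analyses the exclusion applies to.

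Three other places bear on this:

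- **Aim.** The Background states: "This study aims to assess the efficacy and safety of the addition of SMI to conventional therapy".
- **Definition and recording.** Under Safety, "any adverse event will be regarded as serious if it results in death, is life-threatening, requires hospitalization or prolongation of existing hospitalization", with lasting disability or incapacity also counting. The same section says: "All details of AEs, such as time of occurrence, severity, management, and causality to the intervention, will be recorded on case report forms". Events are followed to resolution, and severe ones go to the safety committee and the ethics committee within 24 hours.
- **Known reactions.** Also under Safety, a systematic review of Shenmai injection (SMI) is reported as finding that "ADR cases were mainly systemic reactions (allergic shock), skin lesions (urticaria and pruritus), and local pain".

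Quality control and trial management adds that the Data Monitoring Committee reviews safety data, that reasons for withdrawal are documented, and that the dropout rate is analysed.

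**The concern.** Intention-to-treat keeps every randomised patient. The exclusion rule removes patients because of something that happened after randomisation, and its first trigger is a serious adverse event, which is itself a safety outcome. A safety analysis that drops patients for having the outcome cannot estimate how often it occurs or compare the arms on it.

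Safety is a stated aim, and the reactions the protocol singles out include allergic shock. Such a reaction would meet the protocol's definition of serious if it were life-threatening or lengthened the hospital stay, and would then trigger the exclusion. Patients are recruited from inpatient oncology wards during chemotherapy for advanced disease, so serious events unrelated to SMI are also plausible in both arms.

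This is not a detail left to a later document. The protocol states a rule, and an analysis plan that handled safety properly would have to depart from it.

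**Working it through.** The protocol gives no expected serious adverse event rate, so there is no figure of its own to reproduce. The check compares the two instructions and then shows when the difference matters.

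**1. The two instructions side by side**

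| | Intention-to-treat sentence | Exclusion sentence |
|---|---|---|
| Analyses covered | Efficacy and safety, both named | None named; the object is simply the patient's data |
| Patient with a serious adverse event | Kept | Removed |
| Limited to efficacy or per-protocol? | No | No |

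Both cannot be carried out on the same safety data set.

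**2. Consequence if the exclusion prevails**

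Let x be the number of patients with a serious adverse event in an arm of n. The rule removes all x, so the analysed result is 0 out of at most n − x, for every x and in both arms.

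**3. How likely it is that anyone is affected**

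Input: n = 47 per arm (Sample size estimation). The rates p are assumptions. The expected number is np, and the chance of at least one is 1 − (1 − p)^47.

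| Assumed rate p | Expected patients per arm | Chance of at least one | Analysed count under the exclusion |
|---|---|---|---|
| 2% | 47 × 0.02 = 0.9 | 61% | 0 |
| 5% | 47 × 0.05 = 2.4 | 91% | 0 |
| 10% | 47 × 0.10 = 4.7 | 99% | 0 |
| 15% | 47 × 0.15 = 7.1 | more than 99.9% | 0 |

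**4. What a zero would mean**

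If all 47 patients in an arm were analysed and none had a serious event, the exact one-sided 95% upper limit for the rate would be 1 − 0.05^(1/47) = 6.2%. A zero produced by exclusion supports no such limit, because it would appear whatever the true rate.

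**5. Patients who stop early**

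The Intervention group section gives one infusion a day for 5 days. The protocol article does not say how compliance is measured. If it is counted in infusions (an assumption), 4 of 5 is 80% and stays in, while 3 of 5 is 60% and falls below the threshold. A patient who stopped for intolerance after three or fewer infusions would then be removed. Controls have no infusions to miss, so on that measure this route acts in the SMI arm only. The criterion on unwillingness to continue could remove such patients as well.

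**The case against.** The best defence is that the exclusion sentence never mentions safety, whereas the intention-to-treat sentence does, by name. The authors may have meant the exclusion for efficacy or for a per-protocol analysis only. This is a fair reading, and under it every event counts. A reader might infer from the exclusion sentence alone that the trial has settled on dropping serious adverse events from its safety results, so that a zero rate is guaranteed. The documents do not support that: they contain an unresolved contradiction, and the zero follows only if the exclusion overrides intention-to-treat. The defence does not remove the problem, however, because nothing in the protocol says which sentence prevails.

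A second defence is that events are recorded on case report forms, followed to resolution, reported within 24 hours if severe, and reviewed by a committee, while withdrawals are documented and the dropout rate analysed. All of this stands, and it makes an unnoticed safety signal less likely. It protects monitoring and patient oversight, but it does not put the excluded patients back into the comparison between arms.

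Third, the serious-event criterion touches only part of the safety assessment. Non-serious events, laboratory tests, electrocardiography and tolerated reactions in other patients remain, and two of the three main reaction types listed (skin lesions and local pain) need not be serious. So it would be too broad to say that the rule empties the safety analysis.

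**Conclusion.** The point holds as a contradiction that must be resolved before analysis. One paragraph commits to intention-to-treat for safety and also orders the removal of patients with serious adverse events, with no limit on where the removal applies. If the exclusion is followed, the analysed serious adverse event count is 0 in both arms at any true rate, and no between-arm comparison of these events is possible. If intention-to-treat is followed, nothing is lost.

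The size is therefore conditional. The 61% to 99% chances that at least one patient per arm is affected rest on assumed rates of 2% to 10% and on 47 analysable patients per arm. The further loss of early stoppers depends on how compliance is measured. It would go too far to conclude that a falsely reassuring safety report is planned or inevitable. What is established is that an analyst following the exclusion sentence would produce one, and that no other part of the protocol article prevents it.

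**What to change.** Amend the Statistical analysis section to say three things:

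- The dropout-criteria exclusion does not apply to safety.
- Adverse events, serious adverse events and adverse drug reactions are reported by arm on all randomised patients, with no one removed for an adverse event, compliance, withdrawal or deviation. If an all-treated set is preferred, SMI exposure counts from the first infusion, even if partial.
- The exclusion defines only a labelled per-protocol set, used for a sensitivity analysis of efficacy.

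The third item also removes the conflict with intention-to-treat on the efficacy side. The serious-event criterion need not be deleted from that per-protocol definition. Nothing here alters how patients are treated or when treatment stops; it concerns only whose data are analysed.

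The cost is one or two sentences. The events are already to be recorded on the case report forms, so no new data collection is needed.

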### Randomization, allocation concealment, and blinding

Patients who provide informed consent will be randomized into either a treatment group receiving a 5-day SMI regimen plus conventional therapy or a control group receiving only the conventional therapy. A block randomization sequence will be generated by SAS 9.2 (SAS Institute Inc., Cary, NC, USA) in a 1:1 ratio. Treatment assignments will be conducted using a web-based allocation system. Given the nature of the intervention, it is impossible to blind the patients and personnel involved in conducting the programs. Outcome assessors, laboratory technicians, data managers, and statisticians will be unaware of the treatment allocations.

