### Primary outcome

#### Fatigue severity

Fatigue severity will be self-assessed using the Functional Assessment for Chronic Illness Therapy-Fatigue (FACIT-F) subscale at baseline and on day 5. FACIT-F is a well-validated quality-of-life instrument widely used for the assessment of CRF in clinical trials. It consists of 27 general quality-of-life questions divided into four domains (physical, social, emotional, and functional) and the 13-item FACIT-F fatigue subscale [33]. FACIT-F allows patients to rate the intensity of their fatigue and its related symptoms on a scale of 0 to 4 (0, not at all; 4, very much). The total score for FACIT-F is the sum of the four domains (physical, social, emotional, and functional) plus the fatigue subscale.

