### Sample size estimation

The primary endpoint is the fatigue severity self-assessed using the FACIT-F subscale. The sample size is calculated based on the primary endpoint. Previous clinical practice suggests a mean difference (MD) of 4.95 between groups, and the same standard deviation (SD) of 7.28 for each group. Using a superiority test, it is estimated that 38 participants per group are needed to achieve 90% power and a (two-sided) 5% significance level in detecting treatment differences. Thus, the final sample size has been set at a total of 94 patients (47 in each group), assuming a 20% dropout rate.

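### The plan declares intention-to-treat for efficacy and safety, yet excludes patients on post-randomisation events and then calls for multiple imputation; these rules conflict and leave the primary comparison open to bias

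*Protocol article*

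**What the plan says.** One paragraph of the protocol article, under Statistical analysis, contains three rules.

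- Principle: "Efficacy and safety analyses will be conducted according to the intention-to-treat principle".
- Exclusion: "Data for subjects who meet the dropout criteria (i.e., incidence of serious AEs, < 80% compliance with the protocol", then incomplete data judged able to influence the trial, and further "reluctance to continue the study, large error in protocol, or deviation from the protocol) will be excluded".
- Missing data: "Missing values will be implemented by multiple imputations".

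The exclusion is not tied to a per-protocol or sensitivity analysis, and no such analysis set is named anywhere in the article. Quality control and trial management adds only that reasons for withdrawal are documented and the dropout rate is analysed.

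Other sections bear on the consequences. On blinding, the article says "it is impossible to blind the patients and personnel involved in conducting the programs"; outcome assessors, laboratory technicians, data managers and statisticians are to be kept unaware of allocation. The primary outcome is patient-reported: "Fatigue severity will be self-assessed using the Functional Assessment for Chronic Illness Therapy-Fatigue (FACIT-F) subscale at baseline and on day 5". The Shenmai (SMI) arm receives a daily infusion for 5 days on top of conventional therapy, and the control arm receives conventional therapy only. The sample size rests on "a mean difference (MD) of 4.95 between groups, and the same standard deviation (SD) of 7.28 for each group", with 47 patients per group after a 20% dropout allowance.

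**The concern.** Every listed criterion is an event after randomisation. Removing patients on such events gives up the comparability that randomisation provides, and the result is no longer an intention-to-treat estimate whatever it is called. Protocol deviation carries no severity qualifier, so in principle any deviation is enough.

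Three things are at stake.

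1. **The primary comparison.** Exclusions could plausibly differ between arms. The trial is open-label, the outcome is self-reported, and only the SMI arm has an added infusion and the product-specific reactions described under Safety.
2. **Missing data.** Withdrawal and influential incomplete data are grounds for removal, so many of the patients whose missing primary outcome imputation should serve would already be gone.
3. **Safety.** The paragraph covers safety as well as efficacy. Read literally, a patient with a serious adverse event is dropped from the analysis meant to describe such events, although safety is a stated aim of the trial.

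**Working it through.** **Consistency of the rules**

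| Patient | Intention-to-treat | Exclusion sentence | Imputation sentence |
|---|---|---|---|
| Withdraws, no day-5 score | keep | remove | impute |
| Low compliance, day-5 score present | keep | remove | not needed |
| Serious adverse event | keep, efficacy and safety | remove | only if score missing |
| Any protocol deviation, score present | keep | remove | not needed |
| Minor gaps that could not influence the trial | keep | keep | impute |

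The rules agree only in the last row.

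**Why exclusions could differ by arm.** If compliance were counted by infusions, 3 of 5 is 60% (below 80%) and 4 of 5 is 80% (not below). Only SMI patients have infusions to miss. The article does not say that compliance is counted this way.

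**Inputs for the size of the bias**

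- From Sample size estimation: SD 7.28, target difference 4.95, 47 per group, 20% dropout. The allowance applies to both groups: 38/0.8 = 47.5, stated as 47. (The 38 does not itself reproduce for a two-sided 5% test at 90% power, which needs 46 per group, or 47 by the t distribution. That is a separate matter and nothing below uses the 38 as an input.)
- Assumed, not in the article: no true effect; a fraction f of each arm is excluded; excluded patients score k SD worse than retained ones, with the same k in both arms; SD among retained patients stays at 7.28.

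**Formulas**

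The arm mean equals the retained mean minus f × k × SD, so the retained mean overstates the arm mean by f × k × SD. Hence

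bias = (f_SMI − f_control) × k × 7.28

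SE = 7.28 × √(1/n_SMI + 1/n_control), with n = 47 × (1 − f) rounded

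two-sided type I error = Φ(−1.96 + bias/SE) + Φ(−1.96 − bias/SE)

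**Results**

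| f SMI | f control | k | n | Bias (points) | % of 4.95 | SE | Type I error |
|---|---|---|---|---|---|---|---|
| 20% | 20% | 1 | 38, 38 | 0 | 0% | 1.670 | 5.0% |
| 20% | 10% | 1 | 38, 42 | 0.73 | 15% | 1.630 | 7.3% |
| 10% | 0% | 0.5 | 42, 47 | 0.36 | 7% | 1.546 | 5.6% |
| 10% | 0% | 1 | 42, 47 | 0.73 | 15% | 1.546 | 7.6% |
| 20% | 0% | 0.25 | 38, 47 | 0.36 | 7% | 1.588 | 5.6% |
| 20% | 0% | 0.5 | 38, 47 | 0.73 | 15% | 1.588 | 7.4% |
| 20% | 0% | 1 | 38, 47 | 1.46 | 29% | 1.588 | 15.0% |

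Last row in full: 0.20 × 1 × 7.28 = 1.456; 1.456/4.95 = 29%; 1.456/1.588 = 0.917; Φ(−1.043) + Φ(−2.877) = 0.148 + 0.002 = 0.150. A noncentral t calculation gives 0.148.

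Swapping the fractions reverses the sign: 10% excluded from SMI and 20% from control with k = 1 gives −0.73 points, against SMI.

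**The case against.** The strongest defence is that a journal article condenses the full protocol, and that a full analysis plan may confine the exclusion to a per-protocol set. This does not remove the point. The article states the exclusion outright, for all data, beside the intention-to-treat claim. A later plan could not honour the paragraph; it would have to overrule one of its sentences.

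Other objections do stand, and they limit what can be claimed. A reader might infer each of the following, and the article does not support them.

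- *Controls cannot fail the compliance criterion.* The criterion is compliance with the protocol, not with infusions. Controls also have conventional therapy, two assessments, questionnaires and blood samples. The SMI arm has more ways to fail, which is all that can be said.
- *Unblinded staff decide what counts as a deviation.* No section says who applies the criteria, and data managers and statisticians are to be blinded. The adjudicator is simply unspecified.
- *The bias favours SMI.* In an open-label add-on trial, controls may be the ones reluctant to continue, and removing poorly faring controls would bias against SMI. Serious adverse events can arise in both arms, since all patients receive chemotherapy.
- *The planned 20% dropout implies a 15% type I error.* The plan allows 20% in both groups. The 15% needs all exclusions in one arm and a full 1 SD gap.
- *Nothing is left to impute.* Only incomplete data that could influence the trial lead to exclusion. Minor items, secondary questionnaires and laboratory values could still be imputed. The clash is mainly over a missing primary outcome.

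**Conclusion.** The point holds as an internal contradiction that must be resolved before analysis. If the exclusion sentence is applied, the primary analysis is of a selected subset, cannot be described as intention-to-treat, and is open to bias; the safety analysis loses patients with serious adverse events. This conclusion rests on the text alone and needs no assumption.

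The size of the bias is illustrative only. Over the cases shown it runs from 0 to 1.46 points (0 to 29% of the planned difference), with type I error from 5% to about 15%. The upper end is a corner case, and the less lopsided case of 20% versus 10% gives about 0.7 points and 7%. The article gives no information on who would be excluded, so neither direction nor size can be stated as fact.

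**What to change.** - Remove the exclusion sentence from the primary efficacy and safety analyses.
- Define the primary efficacy set as all randomised patients in their assigned arm, regardless of compliance, deviation, withdrawal or adverse events.
- Use the day-5 FACIT-F score wherever it can be obtained, including after treatment has stopped, and multiply impute only scores that are truly missing.
- Keep every patient in the safety analysis, including those with serious adverse events.
- Use the listed criteria only to define a secondary per-protocol analysis, fixed before database lock and applied blind to allocation.

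The cost is mainly wording. Collecting day-5 scores from patients who stop early takes some effort, and because recruitment began in December 2017 it should be put in place promptly for the patients still to come. The estimate may be smaller than the one from the selected subset.
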